#### Methods in analysis to handle protocol non-adherence and any statistical methods to handle missing data {20c}

Protocol deviations will be defined in the RETURN main trial monitoring plan and specified as minor or major. For final analyses, the number of participants experiencing each protocol deviation will be presented split by allocation group, along with the numbers with at least one minor deviation, at least one major deviation and at least one deviation of either classification. No formal statistical testing will be conducted. The main approach to analysis of outcomes will follow the intention-to-treat principle.

#### Plans to give access to the full protocol, participant-level data and statistical code {31c}

The main trial protocol will be available. Sharing of fully anonymized patient-level data and statistical code would be considered on request.

### Analysis of psychological variables

Analysis involving psychological variables will be undertaken at 12 and 18 months to investigate differences between intervention and usual care in perceived susceptibility, severity, response efficacy, self-efficacy, fear (MDAS) and intentions. Independent groups *t*-tests will be conducted to test differences between groups in these variables. To control for the increased type 1 error rate due to multiple comparisons, the significance level (*p* < 0.05) will be divided by the number of comparisons (6); this means adopting a significance level of *p* < 0.008 to indicate significant differences between groups. If significant differences in psychological variables are found between groups, mediation analyses will be undertaken. One of two types of mediation analysis will be performed depending on *t*-test results. If differences are only found in intentions, then a simple mediation analysis of intervention>intention>planned dental attendance will be undertaken. If differences are found in any of the other PMT variables then, consistent with PMT proposals, serial mediation will be undertaken: Intervention > PMT variable(s) > Intentions > planned dental attendance. All mediation analyses will be conducted using version 4 of PROCESS macro in SPSS 28 [42].

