#### Baseline assessments

The following data will be collected by participant self-report prior to randomisation:Demographic information:Sex (Male/female/prefer not to say)AgeEthnicitySocio-economic information:Education levelEmployment status:In paid employment: Yes/NoIf not employed whether: currently looking/ student /retired /not able due to disability/ not currently looking/ otherBenefit status: Yes/No/Prefer not to sayOHIP-14: 14-item oral health-related quality of life questionnaire [33]EQ-5D-5L: 5-item generic quality of life questionnaire [34]Modified Dental Anxiety Scale (MDAS): 5-part dental anxiety questionnaire [35]Protection Motivation Theory: questionnaire measuring psychological mediators [36]Susceptibility of developing urgent dental problemsResponse efficacy for attending for planned care – that this would reduce the chance of developing an urgent dental problemSeverity – not attending for planned dental care means they would be at risk of tooth loss, bad breath, or getting an abscessSelf-efficacy of attending for planned dental careIntention to attend for a planned care appointmentSelf-report of halitosis [37]Self-report of bad taste [38]Prescription information—prescription of antibiotics and/or analgesics for dental problems by a dental, GP or A&E or similar centre within the last 6 months.

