#### Protection motivation theory: psychological mediation

The Protection Motivation Theory (PMT) is based on a premise that there are two alternative responses to threats (such as dental pain) which are either protective or adaptive coping strategies, or maladaptive responses such as avoidance or procrastination [39]. PMT predicts that the primary determinant of adaptive coping strategies such as planned dental visiting is whether or not an individual has formed a protection motivation with regard to the focal behaviour: for example, an intention to act to manage a health threat (e.g. dental pain). This is in turn informed by parallel appraisal processes: threat appraisal and coping appraisal. Threat appraisal variable predictors comprise perceived severity (seriousness) of the health threat, perceived susceptibility (vulnerability) and fear of the health threat. Applied to dental attendance, patients will be asked to consider the severity of their dental pain and their susceptibility for experiencing dental pain. In order to minimise participant burden; MDAS scores will be used as an indicator of fear of the health threat [35]. Coping appraisal variables comprise self-efficacy (i.e. confidence in performing the focal behaviour) and response efficacy. Applied to dental attendance, patients report their confidence they can attend dental appointments and that such attendance would be an effective way to reduce the threat of dental pain

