### Data collection and management

#### Plans for assessment and collection of outcomes {18a}

Table 1 provides a summary of procedures and assessments relative to participant timelines. Patients receiving dental care in an NHS dental practice following baseline will have a centrally held record in data held by NHS BSA, which will require participant IDs collected at baseline to be matched with participant NHS BSA identifiers. To maximise matching of participant descriptors with routinely held NHS BSA follow-up data, participant postcodes will be checked at each follow-up point in case this has changed since baseline. For participants receiving dental care in the Dental Hospital (DH) following their baseline data, details will be retrieved from clinical records held in the Dental Hospital identified by their unique RQ number. This follow-up data will be collected using a CRF proforma and conducted as an audit of participant DH records. Follow-up data collected by telephone calls by the central research team will be audiotaped and 10% checked by a different researcher than the researcher entering the data during the telephone call. Where disagreements are identified, these will be addressed and resolved by agreement, and any data entry errors rectified. Data collection forms can be obtained from the research team.

**Table 1 Tab1:** Schedule of processes and assessments

Procedures		Screening /Baseline	RETURN Intervention Group	Control Group	Follow-up		
					6 months (+/− 4 weeks)	12 months (+/− 4 weeks)	18 months (+/− 4 weeks)
Assessment of Eligibility Criteria		X					
Signed consent form		X					
Urgent dental treatment (trial processes and intervention around delivery of urgent care)		(X)	(X)	(X)			
Collection of Contact Details, including Home Postcode (to determine IMD as a mediator)		X					
Verification of NHS BSA Matching Descriptors					X^d^	X^d^	X^d^
Collection of RQ6 number^a^		X					
***Self-Reported Assessments***	Socio-economic status (Education level, employment and benefit status)	X			X^b^	X^b^	X^b^
	Age	X					
	Gender (including ‘prefer not to say’)	X					
	Ethnicity	X					
	OHIP-14	X			X	X	X
	Halitosis and Bad Taste	X			X	X	X
	EQ-5D-5L questionnaire	X			X	X	X
	Protection motivation theory questionnaire	X	X^c^	X^c^	X	X	
	Modified dental anxiety scale (MDAS)	X			X	X	X
	Use of Routine Dental Practices and Type (NHS or Private)	X			X	X	X
	Use of Student Teaching Pathway (Dental Hospitals)	X			X	X	X

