	Use of Dental Care Practices, including access centres)	X			X	X	X
	Attendance at a dental service at baseline, and any subsequent urgent, or planned, dental care at follow-up	X			X	X	X
	Use of General Medical Practice for Urgent Dental Care	X			X	X	X
	Use of A&E for Urgent Dental Care	X			X	X	X
	Hospital In-patient Care for Dental Problems	X			X	X	X
	Hospital Out-patient Care, including Dental Hospitals	X			X	X	X
	Prescription of antibiotics and/or analgesics within the last 6 months	X			X	X	X
	Health Economics Participant Questionnaire (including cost of dental treatment, expenses due to dental care, days off work, travel expenses, non-prescription medications [CSRI])				X	X	X
Participant randomised and allocation provided		X					
Administration of RETURN Intervention			X				
Record Intervention Delivery Timing (before, or after, urgent care treatment)			X				
Participant’s Goal and Action Plan			X				
Participant ‘Thank you’ video			X	X			
Participant Voucher Reimbursement			X	X	X	X	X
***Dental team***	Date of urgent dental care visit, participant sex and date of birth.	X					

^a^Participants recruited in Dental Hospital only

^b^Employment status only

^c^RETURN Intervention and Control Groups will complete second protection motivation theory questionnaire after being shown the Thank you video

^d^Participant name, date of birth and postcode. If participant postcode has changed from baseline, then the month that the participant changed their address will also be collected

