#### Adverse event reporting and harms {22}

An adverse event (AE) is classified as one occurring between randomisation and the final follow-up contact at 18 months and is any untoward occurrence which does not necessarily have a causal relationship with the RETURN intervention. Serious adverse events (SAE) are AE which results in death, is life threatening, or is life changing. A related AE is that which is deemed to be a result from administration of research procedures. Due to the type of intervention, SAEs and related adverse events are not expected. However, it is possible that administration of the intervention may lead to increased dental anxiety. Modified Dental Anxiety Scale (MDAS) [35] scores are collected at baseline, 6, 12 and 18 months. MDAS items are summed together to produce a total score ranging from 5 to 25 with higher scores relating to higher levels of dental anxiety [35]. If there is a shift from an MDAS quintile of 0-5/6 (low dental anxiety) at baseline to 19-25 (very high) at 6, 12 or 18 months, this will be reported as an AE. At each site there will be a designated investigator named on the ‘signature list and delegation of responsibilities log’ who is responsible for reporting SAEs and making decisions as to whether this constitutes a SAE and whether this is related or unrelated to trial conduct or intervention, and whether unexpected or not.

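### Psychological variables are to be compared at 12 and 18 months, but five of the six are not collected at 18 months, and the 12-month values come after nearly all the attendance they should explain

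*Protocol article*

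**What the plan says.** The section Analysis of psychological variables states: "Analysis involving psychological variables will be undertaken at 12 and 18 months to investigate differences between intervention and usual care". The variables are "perceived susceptibility, severity, response efficacy, self-efficacy, fear (MDAS) and intentions". Each is compared between groups by an independent-groups t-test, with 0.05 divided by six to give 0.008.

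Mediation follows only if a difference is found. If intentions alone differ, the model runs from intervention through intentions to planned attendance. If any other variable differs, the model is serial: intervention, PMT variable(s), intentions, attendance.

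The measurement schedule is in Table 1 under Plans for assessment and collection of outcomes {18a}:

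- The row "Protection motivation theory questionnaire" is marked at baseline, in both group columns, at 6 months and at 12 months. The 18-month cell is empty.
- Footnote c explains the group columns: "RETURN Intervention and Control Groups will complete second protection motivation theory questionnaire after being shown the Thank you video".

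Five of the six variables come from that questionnaire. Baseline assessments lists susceptibility, response efficacy, severity, self-efficacy and intention under "Protection Motivation Theory: questionnaire measuring psychological mediators". The sixth, fear, comes from elsewhere: "MDAS scores will be used as an indicator of fear of the health threat". For MDAS, Adverse event reporting and harms {22} says that "scores are collected at baseline, 6, 12 and 18 months".

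Attendance is counted within 12 months for the primary outcome and within 18 months for a secondary outcome, from BSA records.

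**The concern.** There are two problems. First, the analysis section names a time point at which the schedule collects almost none of the variables. This is a stated plan that disagrees with a stated schedule, not a detail left for the statistical analysis plan.

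Second, a mediator has to come before the outcome it explains. By the 12-month contact, a participant who was going to attend in the first year has nearly always done so. Having attended may itself raise self-efficacy, response efficacy or intention. An association between 12-month beliefs and attendance within 12 months can then run in either direction, and a mediation model cannot separate the two. Because the t-tests also decide which mediation model is fitted, the timing affects model choice as well as the estimate.

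At stake is the secondary objective of identifying the psychological factors that mediate any effect. A questionnaire completed on the day by both groups is already scheduled, but the analysis section gives it no role.

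**Working it through.** **1. The plan's own figure.** 0.05/6 = 0.00833, stated as 0.008. This reproduces, and it matches six tests at one time point: 6 × 0.008 = 0.048.

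**2. Comparisons implied and comparisons possible.** Six variables at two times make 12. Setting the analysis section against Table 1:

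| Variable | Source | 12 months | 18 months |
|---|---|---|---|
| Susceptibility | PMT questionnaire | yes | no |
| Severity | PMT questionnaire | yes | no |
| Response efficacy | PMT questionnaire | yes | no |
| Self-efficacy | PMT questionnaire | yes | no |
| Intentions | PMT questionnaire | yes | no |
| Fear | MDAS | yes | yes |

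Seven of the 12 have scheduled data and five do not. The blank does not look like a broken table: the neighbouring EQ-5D-5L and MDAS rows are marked at 18 months.

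**3. Order of mediator and outcome.** The article sets 12 months = 52 weeks and 18 months = 78 weeks, and Table 1 allows ± 4 weeks.

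- 12-month mediator: weeks 48 to 56.
- Attendance within 12 months: weeks 0 to 52. At the earliest contact 4 of 52 weeks remain; from week 52 onwards none do.
- Attendance within 18 months: weeks 0 to 78. A mediator at week 52 follows the first 52 weeks and precedes the last 26.
- Post-video questionnaire: completed in the dental setting by both groups, so it precedes later attendance.

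**4. Where the 6-month measurement falls.** The 6-month contact is at week 26 ± 4, that is weeks 22 to 30. Sample size {14} reports that 16% returned for planned care within 22 weeks and expects 30% over 12 months. 16/30 = 0.53, so roughly half of expected first-year attendance may precede the 6-month questionnaire. This assumes that the 16%, from an evaluation of urgent care in dental practices, carries over to this trial's control group.

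**5. Multiplicity.** For k independent tests at 0.008 the family-wise error is 1 − 0.992^k:

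- k = 6: 4.7%
- k = 7 (the tests with data): 5.5%
- k = 12: 9.2%

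For five variables at one time point, 0.05/5 = 0.01.

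**The case against.** **The time points may mean the analysis horizon.** Health economics analysis uses the same phrasing for an analysis that draws on data from baseline onwards, and BSA attendance is defined at exactly those two horizons. Read that way, ending PMT collection at 12 months is coherent and earlier values could be the mediators. The reading is possible but strained, because the sentence goes on to say that group differences in these variables are what is investigated. If it was intended, the article does not say which of the post-video, 6-month or 12-month values enters the model. The unseen statistical analysis plan may say.

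**A reader might infer that the post-video and 6-month measurements will go unused.** The article does not support that; it is silent on their role. Nor is the 6-month measurement safely in the right order, given the 16% against 30%.

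**A reader might infer that a false indirect effect is likely whenever attendance changes beliefs.** The t-test gate argues against this. With 472 per group (590 × 0.8), the standard error of a standardised difference is √(2/472) = 0.065, so p < 0.008 needs about 2.65 × 0.065 = 0.17 SD. If attendance alone moved beliefs, the group difference would be the attendance difference (9 to 10 percentage points) times the shift in attenders. Reaching 0.17 SD needs a shift of 1.7 to 1.9 SD. A shift of 0.5 SD would pass the gate about 2.5 to 3% of the time per variable, and a shift of 1 SD about 10 to 13%. This part of the objection stands. What remains is that, once the intervention truly changes a belief, the gate is passed and the path from mediator to attendance is still open to reverse causation.

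**The matter is secondary.** This also stands: the sample size, both co-primary analyses and safety monitoring are untouched.

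**Conclusion.** The concern holds in limited form. The analysis section and Table 1 contradict each other at 18 months: 5 of 12 implied comparisons, including intentions, have no scheduled data. On the plain reading, the 12-month mediators follow essentially all of the attendance counted within 12 months, so mediation cannot be separated from attendance changing beliefs. They do precede attendance in months 12 to 18.

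Two stronger statements are tempting and should not be made. The first is that half the analysis has no data; the count is 5 of 12, and all six variables exist at 12 months. The second is that the divisor of six lets family-wise error rise to 9.2%. That figure needs 12 tests, and only seven can be run, giving about 5.5% if they are independent. Related constructs, and MDAS measured twice, make independence doubtful. The multiplicity point is minor.

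The conclusion rests on taking the stated months as measurement times. Under the horizon reading the 18-month contradiction disappears, and what remains is that the article names neither the mediator measurement nor the attendance window. The point should be corrected, but it affects one secondary objective and is not critical.

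**What to change.** Change the wording of the analysis section before unblinded data are seen:

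1. Reconcile it with Table 1 by deleting 18 months for the five PMT questionnaire variables.
2. Name the post-video questionnaire, in both groups and adjusted for its baseline value, as the primary mediator measurement, with BSA planned attendance within 12 months as the outcome. The baseline adjustment replaces the unadjusted t-test at that point.
3. Test the five variables available then at 0.05/5 = 0.01. Dividing by six would be wrong there, because Table 1 schedules no post-video MDAS.
4. Treat 6-month values, including MDAS for fear, as supportive, and say that attendance before the contact may have altered them.
5. Report 12-month PMT differences, and 12- and 18-month MDAS differences, descriptively.

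No new data collection is needed. There are two costs. In the serial model the PMT variables and intentions are measured at the same moment, so their order rests on theory. Fear also drops out of the primary mediation set.

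Using 6-month intentions with attendance only after month 6 would not be a better answer. On the article's figures it discards about half of expected first-year events, and it uses intentions that earlier attendance may already have changed.

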#### Secondary outcomes

Attendance at a dental practice for a planned care appointment, self-reported from phone calls at 6, 12 and 18 months.Attempt to make a planned care appointment, self-reported from phone calls at 6, 12 and 18 months.Attendance at a dental practice for a planned care appointment within 18 months, collected from BSA data.Self-reported oral health-related quality of life, measured by the final value at 6 and 18 months adjusting for the baseline value, of the summary score of OHIP-14 [33].Urgent attendance for dental care at dental practice, A&E or Dental Hospital. Patient self-reported at 6, 12 and 18 months.Halitosis and bad taste, measured by patient self-report at 6, 12 and 18 months.Treatment received, as measured by BSA clinical dataset, Dental Hospital audit and patient self-report at 6, 12 and 18 months.Antibiotic prescription by dentists, measured by BSA data, Dental Hospital audit and patient self-report at 6, 12 and 18 months.Antibiotic prescription by GP/A&E/Walk-in centre measured by patient self-report at 6, 12 and 18 months.Analgesic prescription, measured by patient self-report and Dental Hospital data at 6, 12 and 18 months.(safety): Dental anxiety, as measured by the change in the continuous score of the Modified Dental Anxiety Scale (MDAS) [32] recorded in patient self-report at 6, 12 and 18 months.Incremental cost-effectiveness ratio at 12 and 18 months derived from BSA data, patient self-report resource use and EQ-5D-5L at baseline, 6, 12 and 18 months.

Where an outcome measure (secondary outcomes 7, 8 and 10) using data from different sources produces conflicting results, e.g. NHS BSA and patient self-reports on treatment received, the outcome will be recorded as being present if recorded by either data source. Patient self-report of dental services used will include private as well as NHS services, whereas BSA data only records NHS services used.

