### Statistical methods

#### Statistical methods for primary and secondary outcomes {20a}

An extract of the NHS BSA data will be obtained after 12 months (52 weeks) of recruitment. This will aid in the preparation of analysis code before receiving the 18-month (78 weeks) data. Final analysis of the first primary outcome will be conducted on the 18-month data. Analysis of the first primary outcome will involve the number and percentage of participants found to have a planned dental appointment within 12 months which will be reported for each treatment group separately. The denominator will be the number of randomised participants in each treatment group. A comparison between groups will be done using logistic regression, adjusted for the stratification factor site as a random effect (random intercept only). The derived binary variable for attendance for a planned appointment within 12 months will be the dependent variable. The odds ratio and corresponding 97.5% confidence interval will be reported and *p*-value. A sensitivity analysis will be conducted removing all participants from the above primary analysis who were recruited in dental practices (i.e. not randomised at the Dental Hospital) and who do not have a matched NHS BSA record at baseline. This is to assess the impact of including the participants who were not successfully matched in the NHS BSA data at baseline which may indicate that it was possible to get NHS BSA data at later timepoints.

Analysis of the second primary outcome will involve summaries of OHIP-14 scores presented at baseline and 12 months separated by treatment group, for all participants included in this analysis. The OHIP-14 scores at 12 months will be analysed using linear regression, adjusting for the baseline value of OHIP-14 and the stratification factor site as a random effect (random intercept only). The estimated treatment effect and corresponding 97.5% CI will be reported along with the *p*-value. This will be a complete case analysis, only participants with valid baseline and 12-month questionnaires will be included in the analysis.

A second analysis will also adjust for other pre-specified baseline variables, including dental anxiety and socio-economic status.

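### The t-tests that gate the mediation analysis ignore baseline values and site, giving up power that the trial's own OHIP-14 model would recover

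*Protocol article*

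**What the plan says.** The section Analysis of psychological variables names six variables and fixes the method: "Independent groups *t*-tests will be conducted to test differences between groups in these variables". It divides 0.05 by six comparisons, "adopting a significance level of *p* < 0.008 to indicate significant differences between groups".

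The results have consequences. First, "If significant differences in psychological variables are found between groups, mediation analyses will be undertaken". Second, "One of two types of mediation analysis will be performed depending on *t*-test results": a simple model if only intentions differ, a serial model through the other Protection Motivation Theory (PMT) variables and then intentions if any of those differ. Identifying psychological mediators is listed under Secondary objectives.

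The section Baseline assessments opens with "The following data will be collected by participant self-report prior to randomisation", and its list includes the PMT items, intention and MDAS. All six variables therefore have a pre-randomisation value. Randomisation is stratified by site (Sequence generation {16a}).

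For OHIP-14 at 12 months, Statistical methods {20a} specifies a linear regression "adjusting for the baseline value of OHIP-14 and the stratification factor site as a random effect". Secondary outcomes likewise takes OHIP-14 at 6 and 18 months as a final value adjusted for baseline.

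**The concern.** A two-sample t-test on the follow-up value leaves in the error term all the between-person variation that the baseline value could explain. The trial collects that baseline value for every variable tested and already uses the more efficient model for OHIP-14. The article gives no reason for treating the psychological variables differently.

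In a purely descriptive comparison this would be a small matter. Here the tests are run at a strict level and act as a switch. A missed difference can leave a variable out of the mediation model or select the simple model where the serial one was warranted. If all six tests miss, no mediation analysis is done. Power lost at this step therefore bears on a named secondary objective. Neither primary analysis is affected.

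**Working it through.** **The plan's own figures.** The article states no power for the psychological tests. The nearest stated figure is for OHIP-14 (Sample size {14}): SD 11, difference 2.25 points, alpha 0.025, 20% loss from 590 per arm.

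- Evaluable per arm: 590 × 0.80 = 472.
- Power = Φ( (2.25/11)/√(2/472) − z(1 − 0.025/2) ) = 81.6%, against 80% stated. The figure reproduces, so 472 per arm is a fair basis for other telephone-collected measures.

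**Inputs for the psychological tests.**

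- n = 472 per arm. The 20% loss is stated for OHIP-14; applying it to these questionnaires is an assumption.
- Two-sided alpha = 0.05/6 = 0.00833, so z(1 − 0.05/12) = 2.638. The article rounds this level down to 0.008.
- Effect d = 0.2 SD: assumed, not in the documents.
- Correlation r between baseline and follow-up: assumed, not in the documents. Range shown: 0.3 to 0.7.

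**Formulae.** With the follow-up variance set to 1, the residual variance is 1 for the t-test and 1 − r² after baseline adjustment.

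Power = Φ( d / √(1 − r²) / √(2/472) − 2.638 ), where √(2/472) = 0.0651.

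| Analysis | Residual variance | Standardised effect ÷ SE | Power, one test |
|---|---|---|---|
| t-test | 1.00 | 3.07 | 66.8% |
| Adjusted, r = 0.3 | 0.91 | 3.22 | 72.0% |
| Adjusted, r = 0.5 | 0.75 | 3.55 | 81.8% |
| Adjusted, r = 0.7 | 0.51 | 4.30 | 95.2% |

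At the rounded level of 0.008 the four powers are 66.3%, 71.5%, 81.5% and 95.1%.

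The comparison does not rest on d = 0.2 alone. The t-test has 80% power at d = (2.638 + 0.842) × 0.0651 = 0.227. At that effect the adjusted analysis has 84.4%, 91.6% and 98.7% at r = 0.3, 0.5 and 0.7. No gain from the site term is counted in any of these figures.

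**From one test to the gate.** The gate opens if any of the six tests succeeds. The table below keeps d = 0.2 for each affected variable, and assumes a correlation of 0.5 between the test statistics and r = 0.5 for the adjusted analysis. The chance that at least one affected variable reaches significance is:

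| Variables affected | t-tests | Adjusted | Gain |
|---|---|---|---|
| 1 | 67% | 82% | 15 points |
| 3 | 88% | 96% | 8 points |
| 6 | 94% | 98% | 4 points |

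With a weaker effect of 0.15 SD on all six variables, the figures are 75% and 86%. The gain for the gate as a whole therefore shrinks as more variables respond. The single-test gain still applies to which variables enter and to which model is chosen.

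**The case against.** **Validity.** The t-test is valid under randomisation, and chance baseline imbalance is already reflected in its error rate. This stands: the point concerns efficiency and consistency, not bias.

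**Size.** Neither d nor r is in the documents. At r = 0.3 the gain is only about 5 points (66.8% to 72.0%). This also stands. The direction is certain for any non-zero r; the size is not.

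**A stronger reading of the gate.** A reader might infer that one false negative cancels the mediation analysis. The text does not support that. A difference in intentions alone leads to the simple model and a difference in any other variable leads to the serial model, so mediation is skipped only if all six tests miss. What one miss can do is drop a variable or change the model.

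**A stronger reading of MDAS.** Secondary outcomes defines the safety measure as "Dental anxiety, as measured by the change in the continuous score of the Modified Dental Anxiety Scale (MDAS" score. A reader might infer that the safety analysis is an unadjusted change score with a needlessly wide interval. That wording defines the outcome variable, and the article states no model for it. Change regressed on arm and baseline gives the same treatment estimate and interval as the final value adjusted for baseline. Nor does an outcome definition settle the model elsewhere: Primary outcomes describes OHIP-14 only as its value at 12 months, yet Statistical methods {20a} adjusts for baseline. The safety outcome also gates nothing, since MDAS enters the mediation decision only as fear, through the t-test. No criticism of the safety analysis is made here.

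**The gate remains.** Baseline adjustment does not remove a significance gate, and a null result can still block mediation. True; adjustment only makes a miss less likely.

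**Conclusion.** The point holds for the six t-tests. The article fixes an unadjusted comparison although a baseline value exists for each variable and the trial's own OHIP-14 model shows the better choice. Under the stated assumptions (472 per arm, alpha 0.05/6, 0.2 SD), single-test power is 67% where 72% to 95% is available for correlations of 0.3 to 0.7. At r = 0.5 the chance of missing a real difference in a given variable falls from about 33% to 18%. For the gate as a whole, the gain at r = 0.5 runs from 15 points if one variable responds to 4 points if all six do. It is a worthwhile improvement to a secondary objective and leaves the primary conclusions untouched.

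**What to change.** In Analysis of psychological variables, and in the analysis plan, replace the independent-groups t-tests as follows. For each of the six variables, at each follow-up time at which it is measured, fit a linear model of the follow-up value on arm, that variable's baseline value and a site random intercept, as for OHIP-14. Keep the stated Bonferroni level and the rule linking the results to the mediation models. The wording about measurement times matters because Table 1, as it reads here, marks the PMT questionnaire at 6 and 12 months but not at 18.

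The cost is a change of wording, to be made before the statistical team sees unblinded data. It needs no extra data and places no burden on participants.
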